# Efficacy of two educational interventions about inhalation techniques in patients with chronic obstructive pulmonary disease (COPD). TECEPOC: study protocol for a partially randomized controlled trial (preference trial)

**DOI:** 10.1186/1745-6215-13-64

**Published:** 2012-05-21

## Abstract

**Background:**

Drugs for inhalation are the cornerstone of therapy in obstructive lung disease. We have observed that up to 75 % of patients do not perform a correct inhalation technique. The inability of patients to correctly use their inhaler device may be a direct consequence of insufficient or poor inhaler technique instruction. The objective of this study is to test the efficacy of two educational interventions to improve the inhalation techniques in patients with Chronic Obstructive Pulmonary Disease (COPD).

**Methods:**

This study uses both a multicenter patients´ preference trial and a comprehensive cohort design with 495 COPD-diagnosed patients selected by a non-probabilistic method of sampling from seven Primary Care Centers. The participants will be divided into two groups and five arms. The two groups are: 1) the patients´ preference group with two arms and 2) the randomized group with three arms. In the preference group, the two arms correspond to the two educational interventions (Intervention A and Intervention B) designed for this study. In the randomized group the three arms comprise: intervention A, intervention B and a control arm. Intervention A is written information (a leaflet describing the correct inhalation techniques). Intervention B is written information about inhalation techniques plus training by an instructor. Every patient in each group will be visited six times during the year of the study at health care center.

**Discussion:**

Our hypothesis is that the application of two educational interventions in patients with COPD who are treated with inhaled therapy will increase the number of patients who perform a correct inhalation technique by at least 25 %. We will evaluate the effectiveness of these interventions on patient inhalation technique improvement, considering that it will be adequate and feasible within the context of clinical practice.

**Trial registration:**

Current Controlled Trials ISRTCTN15106246

## Background

Drugs for inhalation are the cornerstone of therapy in obstructive lung disease. Inhalers are the principle vehicles for the effective administration of medication. They allow high lung deposition of the drug and minimize systemic adverse drug reactions [1,2]. The effectiveness of drugs for inhalation can be influenced by many factors including age, sex, education of the patient, duration of disease, type of inhaler used, correct inhalation technique and use of several inhalers [2,3].

There are three main categories of inhalers: pressurized metered dose inhalers (pMDIs), dry powder inhalers (DPIs) and small volume nebulizers (SVNs). DPIs and pMDIs are the devices most commonly used for drug delivery in the treatment of asthma and COPD patients [1,2].

Technical features of inhaler devices have improved over time. However, the effectiveness in delivering drugs to the lung depends on correctly performed inhalation maneuvers. Incorrect usage of inhalers is a significant problem for both asthma and COPD management because it may result in diminished therapeutic effects, resulting in poor control of symptoms and thereby insufficient disease management [4-6]. As a result, patients might receive treatment, but without proper education and training in correct inhalation techniques, the therapeutic benefit is less than optimal [2].

In a previous study, we observed that up to 75 % of patients do not perform a correct inhalation technique (data not published) and other studies show a similar percentage of error [7-9]. Many inhalers are complicated to use and some require up to eight steps [1].

Efficient use of pMDIs requires coordination between simultaneous inhalation and device actuation, a slow and continuous inspiratory flow rate during inhalation followed by a breath hold of at least ten seconds. Patients frequently fail to exhale fully before inhalation, they activate the device before or at the end of inhalation, or while breath-holding. Other common errors are high inspiratory flows, not shaking the device before use and stopping inspiration when the spray collides with the throat. Other drawbacks of these devices are that they contain environmentally unfriendly propellants and most of them provide no dose counter, so the patients do not know the number of doses remaining and they use the device when it is empty [1,9,10].

The use of DPIs removes the coordination problem; however mistakes in the inhalation techniques are high. The most common errors are: not placing the device correctly, exhaling into the mouthpiece, low inspiratory flows and incorrect breath-holding. The most critical mistakes may be exhalation into the mouthpiece and low inspiratory flow, because the humidity and inadequate flow reduce the amount of drug released and its ability to reach the lungs [1,10].

Other factors associated with improper use of devices in patients with COPD are related to age and cognitive status [11,12], the number of devices [10,13] and the training of healthcare professionals. Healthcare personnel responsible for teaching the correct use of inhalation devices are lacking in basic knowledge and user skills [10,14]. To acquire the skills for using these devices, health professionals and patients must be adequately educated and trained [15,16].

The inability of patients to use their inhaler device correctly may be a direct consequence of insufficient or poor inhaler technique instruction. The quality of the initial instruction is of paramount importance for the outcome of inhalation therapy. Written instruction alone is insufficient in teaching correct inhalation techniques. Verbal instruction and technique assessment and reassessment are essential for patients to achieve a proper technique [17]. Patients who receive inhalation instructions at least once more after the initial instruction have better inhalation techniques compared with those who only receive instruction at the time of prescription [18]. Training in correct inhaler use rather than instructor demonstration appears to be important [19,20].

The objective of this study is to test the efficacy of two educational interventions to improve inhalation techniques in patients with COPD.

## Methods

This study has been approved by the Ethical Committees of Distrito Sanitario Málaga (01/03/07) and Axarquía (13/05/08).

### Participants

A total of 495 patients with COPD selected by a non-probabilistic consecutive sampling method from seven Primary Care Centers will participate in the study. The inclusion criteria will be: having been diagnosed with COPD by spirometry following the SEPAR (Sociedad Española de Neumología y Cirugia Torácica) guidelines [21], receiving clinical assistance in primary care centers in the Malaga area, having been prescribed inhalation treatment, and having agreed to be part of the study by giving signed written consent. Exclusion criteria will be: other respiratory conditions which are not included in the COPD definition (bronchiectasis, asthma or cystic fibrosis) and cognitive impairment problems registered in their clinical record (dementia, Alzheimer, Parkinson, cognitive decline). All these criteria will be reviewed in the patients´ clinical record.

### Sample size

This was calculated to detect a correct inhalation technique percentage difference between groups of 25 %, with a statistical power of 80 % and a confidence level of 95 %, assuming a percentage of expected losses of 40 %. The final sample size is 495 patients with COPD who meet the selection criteria mentioned above. In the Randomized group it will be necessary to include 297 patients, and in the Preferences group 198 (99 patients per arm).

### Design

The study is structured as a multicenter patients´ preference trial or a comprehensive cohort design (Figure 1). The patients will be divided into two groups:

Randomized patients: randomized control trial (RCT) group with three arms (control, intervention A and intervention B)

Patients with preferences: PPS group with two arms (intervention A and intervention B)

**Figure 1 F1:**
[figure not shown]
Study general graphic.

Patients without strong preferences for a treatment are randomized and those with strong preferences are given their choice. Such a design enables comparisons between patients with and without a preference and an exploration of patient characteristics associated with preference [22,23].

### Setting

The study will take place in primary care facilities in Malaga, Spain.

### Outcomes

#### Primary outcome

Performance of correct inhalation techniques. The correct inhalation techniques will be measured by an investigator following SEPAR guidelines [1].

#### Secondary outcome

Participants will be evaluated using inhalatory pick flow, functional status (spirometry), mental-cognitive status (Mini-mental Status Examination test), dyspnea with Baseline Dyspnea Index (BDI) [24] and Modified Medical Research Council (MMRC) [25]; questionnaires of quality of life (St George respiratory questionnaire [26], and EuroQoL-5D [27]) and the clinical progress of illness (Seguimiento Clínico en EPOC: SeguiEPOC questionnaire).

#### Independent variables

Independent variables will be: age, sex, educational level, comorbidity, smoking history, COPD severity grade (according to SEPAR guidelines [28]), prescribed medication, family support (Family Apgar Test [29]): and social support (DUKE-UNC Test [30]).

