### Recruitment

Patients will be contacted using their health center records. They will be invited to participate in the study after a brief explanation by telephone about the research aims and they will receive an appointment in the health center. At this first appointment (inclusion visit) patients will receive more detailed information about the study and, if they agree to participate, they will sign the written consent.

At this point, subjects will be asked whether they have a preference for one of the interventions and they will be divided into two groups (Figure 1). Those who select the preference group choose their intervention and they will form two arms of the study. The participants without a preference will join the randomized group and they will be randomly allocated into the three arms of this group.

In the preferences group, the two arms correspond to the two educational interventions designed for this study. In the randomized group the three arms will be: intervention A, intervention B and a control arm.

The randomization will be made using the block randomization technique. The blocks consist of six patients, two subjects per group or three patients, one patient per group (Intervention A, Intervention B and control). The blocks will be marked with a number from 1 to 96 and they will be chosen at random to create the allocation sequence using a sequence of random numbers generated by the Microsoft Excel 2003 program with the function fx:RAND(). The assignment to this group will be made by contacting the person responsible for random sequence by phone. Because the patients are from various health centers, the randomization and the presence of the two interventions and control subjects in all the health centers will be guaranteed.

After randomization all the study data will be recorded and the performance of correct inhalation techniques will be measured in all groups (inclusion visit). In the case of the control group, the inhalation techniques will be tested asking them about how they use their inhalers and the interviewer will write down the mistakes in the template designed. The interviewer will only correct the critical mistakes. In the follow-up visits the subjects will be invited to perform the inhalation technique and the mistakes will be written down.

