### Statistical analysis

A descriptive statistical analysis will be performed for all the study variables. We will calculate the mean, median and standard deviations for quantitative variables, and the absolute and relative frequency for qualitative variables.

The 95 % confidence interval will be applied. The analysis will be made following an intention-to-treat procedure. The baseline comparison will be made between the main variables that we expected to be related to the primary outcome using the Chi-Square test or an analysis of variance (ANOVA).

The between-group comparison for the primary outcome will be explored using the Chi-Square Test. The Relative Risk Reduction (RRR), the Absolute Risk Reduction (ARR) and the Number Needed to Treat (NNT) will be calculated. Inferences for the secondary outcomes will be made using an ANOVA or Chi-Square test. Each group will be analyzed separately. The comparison using PPS groups is unreliable because of the presence of unknown and uncontrolled confounders. It is necessary to make a comparison between RCT groups alone and analyses which include the PPS groups should be treated as observational studies with known confounding factors adjusted for in the analysis. Then the analysis will be performed following the next steps:

Comparison in RCT group: this will be made between each intervention arm versus control arm (intervA versus control; intervB versus control) and between intervention A and intervention B.

Comparison between RCT and PPS groups: this will be performed between the intervention arms of each group (intervA RCT group versus intervA PPS group; intervB RCT group versus intervB PPS group).

Finally, a logistic regression model will be performed for the primary outcome (performance of correct inhalation technique (yes/no)), considering the intervention as the predictive variable and the rest of the independent measures as the possible modifying factors. We will use the usual 5 % significance level (α = 0.05) and the SPSS statistical package, version 15.0, to run the proposed analysis.

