Another important aspect to consider is the protocol and the intervention standardization. This is why the dynamic has been structured in an exhaustive way and the intervention will be performed by two professionals trained in communication, disease knowledge and inhalation techniques of the different devices used by COPD patients. Furthermore, we have designed a manual for the researchers where we explain the working plan, the different parts of the intervention, the protocol scheme to know what they have to measure each time and the details to assess each variable included in the study. In this way, the procedure can be replicated elsewhere.

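### Centre is absent from the primary test and the covariate list: a small loss of precision in the randomized comparisons, and a recordable confounder left open in the randomized-versus-preference contrasts

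*Protocol article*

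**What the plan says.** The Participants section describes patients "selected by a non-probabilistic consecutive sampling method from seven Primary Care Centers". The Recruitment section says of the randomized group that "the presence of the two interventions and control subjects in all the health centers will be guaranteed". It makes no comparable statement for the preference group, whose patients choose at the inclusion visit in their health centre. The Discussion caps each preference arm at 120.

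Under Statistical analysis, "The between-group comparison for the primary outcome will be explored using the Chi-Square Test". The randomized comparisons are A versus control, B versus control and A versus B. Two further contrasts compare randomized with preference patients within intervention A and within intervention B. The section says that analyses including preference patients are observational and need adjustment for known confounders. The one model described is a logistic regression with the intervention and the remaining independent measures. The Independent variables section lists these: "Independent variables will be: age, sex, educational level, comorbidity, smoking history, COPD severity grade", followed by prescribed medication, family support and social support. Centre appears in no test, model or list.

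On delivery, Study limitations states that "the intervention will be performed by two professionals trained in communication, disease knowledge and inhalation techniques". The professional is not in the list either.

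**The concern.** Inhaler technique is taught in person and judged by an observer, so rates of correct technique can plausibly differ between centres. Omitting centre has two different consequences.

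- **Randomized comparisons.** If arms are balanced within centres, a pooled chi-square leaves between-centre variation in the error term. The test stays valid but is less sharp than it could be.
- **Randomized versus preference contrasts.** Here the mix of centres can differ between the two groups. A centre with many choosers and an unusually high or low rate of correct technique shifts the contrast, and the shift could be read as an effect of preference, which is what this design is meant to study. The listed patient characteristics remove it only so far as they happen to explain the centre differences.

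**Working it through.** **1. The plan's sample size.** The Sample size section gives a 25-point difference, 80% power, 95% confidence, 40% losses and 99 per arm. It gives no control rate. I assume 25% correct, the complement of the 75% incorrect reported in the Discussion.

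- Pooled formula, 25% vs 50%: (1.96·√(2·0.375·0.625) + 0.842·√(0.1875 + 0.25))² / 0.25² gives 58 per arm, and 58/0.6 gives 97.
- Unpooled formula, 37.5% vs 62.5%: (1.96 + 0.842)² · 0.46875 / 0.0625 gives 59, and 59/0.6 gives 99.

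The stated figure reproduces. I use 99 × 0.6 ≈ 59 evaluable patients per arm below.

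**2. Randomized comparisons.** The documents give no between-centre variation, so it is assumed. Simulation: seven unequal centres, 8,000 replicates, normal centre effects on the logit scale, marginal rates held at 25% and 50% (37.5% under the null). Each result is chi-square / Cochran-Mantel-Haenszel (CMH) by centre.

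| Centre SD | Balanced: null rejection | Balanced: power | Not balanced: power |
|---|---|---|---|
| 0 | – | – | 81.0 / 78.9% |
| 0.5 | 4.5 / 4.9% | 81.8 / 82.8% | 81.0 / 80.8% |
| 0.8 | 4.1 / 5.0% | 83.0 / 85.2% | 81.2 / 82.9% |
| 1.0 | 3.4 / 4.7% | 82.7 / 86.3% | 81.7 / 84.9% |

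With balanced arms the gain from stratifying is 1.0, 2.2 and 3.6 points. On the latent scale, ICC = SD²/(SD² + π²/3), so these SDs correspond to ICCs of about 0.07, 0.16 and 0.23.

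A separate simulation with seven equal, balanced centres (4,000 runs) covers smaller values:

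| ICC | Power, chi-square / CMH |
|---|---|
| 0 | 82.0 / 81.7% |
| 0.02 | 79.6 / 80.1% |
| 0.05 | 81.3 / 82.1% |
| 0.10 | 82.0 / 83.5% |
| 0.20 | 82.7 / 85.5% |

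The Monte Carlo error is √(0.8·0.2/4000) ≈ 0.6 points, so 79.6% is not a real shortfall from 80%.

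**3. Randomized versus preference, by centre.** The bias is the difference in correct-technique rate between centres times the difference in their share between the groups. For example, 10 points × 0.10 = 1 point, and 20 points × 0.30 = 6 points.

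Simulation at a common 50% rate, 59 per group, with no true preference effect: null rejection is 5.4% when outcome and choosing share both have logit SD 0.5, and 11.0% when both have SD 1.0. Stratified by centre it is 4.5% to 5.4%. A repeat run gave 5.5% to 11.5% unadjusted and about 4.9% stratified.

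**4. Randomized versus preference, by professional.** Assume a 15-point gap between the two professionals, choosers split 60/40 to 70/30, and randomized patients split 50/50.

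- Bias: 0.1 × 15 = 1.5 points to 0.2 × 15 = 3 points.
- Standard error: √(2·0.25/59) = 9.2 points.
- Null rejection: Φ(−1.96 + bias/SE) + Φ(−1.96 − bias/SE), which gives 5.3% to 6.2%.

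**The case against.** **This may be detail for an analysis plan that is not shown.** The article does not exclude centre, and its call to adjust preference analyses for known confounders is not expressly tied to the Independent variables list. It would therefore be too strong to say that the contrasts must stay confounded whatever the analysts do. But the article itself names the test, the model and a list of covariates, and centre is in none of them. The point stands as a correction to what is written.

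**The primary test is valid.** This stands in full. A reader might infer an inflated error rate or an undermined sample size. The calculations show the opposite: with balanced arms the plain test errs on the conservative side and power stays at about 80% or above.

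**The gain depends on balance by centre.** This also stands. Recruitment promises every arm in every centre, but describes randomly drawn blocks without expressly stating stratification by centre. Without balance, CMH gains nothing at SD 0.5 and loses about 2 points at SD 0.

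**The preference contrasts are already qualified.** The article calls them unreliable and observational, and says the pure treatment effect cannot be isolated. That limits the risk of over-reading, but does not justify leaving out a confounder known for every patient.

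**The professional is a weaker case than centre.** A reader might infer that the two professionals assess the patients they taught. The documents do not say so: the outcome is measured by an investigator whose relation to the two is not stated. Nor do they say how the professionals are spread over centres. Training and a researcher manual are meant to reduce differences between them. A bias of 3 to 6 points would need randomized patients to be split in mirror image to the choosers, which nothing in the documents supports.

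**Conclusion.** The concern holds as a modest, cheaply corrected weakness. For the randomized comparisons it is one of efficiency alone: about 0 to 4 power points if arms are balanced by centre, for an assumed centre SD of 0 to 1.0, with no bias.

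The preference contrasts are the main reason to act. With an assumed SD of 0.5 to 1.0 for both outcome and choosing share, the unadjusted false-positive rate is about 5.5% to 11%, against about 5% when stratified. Adjusting for the listed covariates would lower the excess to the extent that they explain centre differences; the documents give no basis for saying how far. The professional adds about 1.5 to 3 points of bias under the stated assumptions.

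All these sizes rest on assumed variation. Adjustment removes only the centre and professional part of the confounding; other differences between choosers and randomized patients remain, as the article concedes.

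**What to change.** - **Independent variables:** add health centre.
- **Statistical analysis, randomized group:** test A vs control, B vs control and A vs B with a Cochran-Mantel-Haenszel test stratified by centre, pooling very small centres. Take the absolute risk reduction and NNT from the Mantel-Haenszel risk difference. Keep the plain chi-square as a sensitivity analysis.
- **Logistic model and randomized-versus-preference contrasts:** include centre.
- **Professional:** record who delivers the intervention at the inclusion visit, so that the variable is not one that changes during follow-up. Add it to the randomized-versus-preference adjustment only if professionals are not nested in centres; otherwise the two effects cannot be separated.

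The cost is a few sentences of analysis wording, one recorded item and no extra patients. The downside is up to about 2 power points in the randomized comparisons (81.0% to 78.9%) if centres do not differ and allocation is not balanced by centre.
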